## 8.6.1.3 Multiple Imputation

As a sensitivity analysis of the primary and key secondary dichotomous efficacy endpoints (e.g. ACR50 responder), multiple imputation of missing data will be performed and analyzed using logistic regression. Multiple imputation uses a simulation based approach, replacing missing values from multiple draws from conditional distributions given the observed data and covariates. Assuming an arbitrary missing data pattern the missing values for each component will be imputed separately based on a fully conditional specification (FCS) approach, this method uses all variables in the imputation model for any other variable.

The imputations will be done using the corresponding baseline value, sex and exposure to biologic agents at baseline as covariates. If there are any missing values in those variables they will also be imputed, in the model a single component at a specific visit, will consider all previous visits as covariates. The full conditional specification regression model will be used for continuous variables and the number of imputations will be 100 with 50 burn in imputations and the seed for all imputations will be 4278491. For all visit results a minimum value of 0 will be added to the imputation. If the imputation does not input values within the specified range then the number of maximum iterations by step will be increased accordingly.

For each completed imputed dataset, the necessary derived variables will be computed using logistic regression as described in section 8.6.1.1 and the results obtained will be combined into one multiple imputation inference using proc MIANALYZE.

The SAS pseudo code for this imputation process is listed below:

[figure not shown]

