5.5 Sample Size and power

The sample size calculation is based on the primary efficacy endpoint (i.e., ACR50 response rate at Week 12 compared with baseline) with the primary comparisons of interest being:

sonelokimab 120 mg Q2W (Arm 1) vs placebo (Arm 4), sonelokimab 60 mg Q2W (Arm 2) vs placebo (Arm 4) and sonelokimab 60 mg Q4W (Arm 3) vs placebo (Arm 4) and determined based on assumed ACR50 response rates as follows:

- 40% with each sonelokimab dose regimen;
- 10% with placebo.

The estimated response rates for sample size were based on past IL-17 inhibitors for the treatment of participants with PsA. The Cosentyx FUTURE 2 study showed that ACR50 was achieved in 35% of secukinumab 300 mg and 37% of secukinumab 150 mg, vs 6% in the placebo arm [McInnes I.B. et al., 2015].

A sample size of n = 40 participants in each of the sonelokimab 120 mg Q2W, sonelokimab 60 mg Q2W, sonelokimab 60 mg Q4W and placebo arms (therefore, 160 participants in total) results in a power of more than 80%, while assuming an overall 2-sided alpha of 0.025, a placebo ACR50 response rate of 10% and a difference in ACR50 response rate of 30% between placebo and each sonelokimab dose regimen. An additional 40 participants will be randomized in the adalimumab arm. The adalimumab treatment will be used as an active reference arm, however, no formal comparison of sonelokimab or placebo vs adalimumab is planned.

Eligible participants will be randomized in a 1:1:1:1:1 ratio to sonelokimab 120 mg Q2W (Arm 1), sonelokimab 60 mg Q2W (Arm 2), sonelokimab 60 mg Q4W (Arm 3), placebo (Arm 4) or adalimumab 40 mg Q2W (Arm 5). The total proportion of participants with previous use of biologic agents will be capped at 30%.

Due to the use of the FAS with non-responder imputation, no accounting for dropout is required, therefore a total of approximately 200 participants will be randomized.

All calculations were performed in nQuery® Software version 8.5.1.0.

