### 8.6.2.1 American College of Rheumatology 50 Clinical Response

The ACR50 will be assessed at Week 2, Week 4, Week 8, Week 12, Week 14, Week 16, Week 20 and Week 24 however the primary endpoint is the proportion of ACR50 responders at Week 12.

ACR50 response criteria is defined as:

- ACR50 Responder: *participant who had improvement in the ACR response criteria  $\geq 50\%$ ;*
- ACR50 Non-responder: *Otherwise.*

ACR50 response is:

- At least a 50% improvement in TJC68;
- At least a 50% improvement in SJC66;
- At least a 50% improvement in at least 3 of the following 5 variables:

- PtAAP;
- PtGADA;
- PhGADA;
- HAQ-DI;
- hs-CRP.

A Non-responder imputation method will be used for all missing data for the primary estimand as detailed in [section 7.3.2](#).

The null hypotheses to be tested are that the proportion of ACR50 responders at Week 12 are no different for the following comparisons:

- sonelokimab 120 mg Q2W versus placebo
- sonelokimab 60 mg Q2W versus placebo
- sonelokimab 60 mg Q4W versus placebo

To test these hypotheses, a pairwise stratified logistic regression will be used as detailed in [Section 8.6.1.1](#). This analysis will also be conducted for Weeks 2, 4 and 8.

The data for Part B will be presented by FAS-Part B and will be split by Part A and Part B treatment.. Non-responder imputation and As-Observed summaries will be presented. No statistical analysis will be presented. These results will also be presented in a line plot.

The following sensitivity analysis of the Part A data will be presented:

- the first sensitivity estimand will be analysed using logistic regression, with the same covariates as for the primary analysis. Missing data will be imputed as described in [section 5.2](#) with multiple imputation applied as described in [8.6.1.3](#) such that subjects who had prohibited medication or discontinued due to efficacy or adverse events are set as non-responders, all other missing data is imputed with multiple imputation methods.
- the second sensitivity estimand will be analysed using logistic regression, with the same covariates as for the primary analysis [with multiple imputation applied as described in 8.6.1.3](#)
- An observed analysis using logistic regression model but with no imputation of missing data.

Line plots for ACR50 response rate by week will also be provided, with week on the x axis and ACR50 response rate on the y axis. Graphs for Part A and Part B (FAS) will be presented.

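### As worded, the multiple-imputation model handles ACR components separately and lists no treatment term; if implemented that way, it pulls the arms together in the sensitivity analyses

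*Combined protocol and SAP*

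**What the plan says.** SAP 8.6.1.3 describes the imputation for the primary and key secondary dichotomous endpoints. It states that "the missing values for each component will be imputed separately based on a fully conditional specification (FCS) approach", and then that "The imputations will be done using the corresponding baseline value, sex and exposure to biologic agents at baseline as covariates". It adds that a single component at a given visit takes all previous visits as covariates. It also remarks that the fully conditional method lets every variable in the model inform every other one. The paragraph never names treatment. It ends by introducing SAS pseudo code, which is not shown in the supplied text.

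SAP 8.6.2.1 applies this model to both sensitivity estimands for ACR50. Under the first, prohibited medication and discontinuation for lack of efficacy or an adverse event count as non-response, and "all other missing data is imputed with multiple imputation methods". The second, a treatment-policy estimand, uses the same imputation without those exceptions. SAP 8.6.3.1 and 8.6.3.2 carry the approach over to ACR20 and PASI90.

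The primary analysis uses non-responder imputation (SAP 7.3.1, 8.6.2.1). A third sensitivity analysis uses observed data only. SAP 8.6.1.4 classes all sensitivity analyses as exploratory.

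**The concern.** Two features of the wording matter.

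- **Joint criterion.** ACR50 requires TJC68, SJC66 and at least three of five further measures to improve by half in the same participant. If measures missing at the same visit are drawn from unconnected models, their correlation is lost and joint improvement becomes too rare among imputed participants.
- **Treatment omitted.** The analysis model compares arms (SAP 8.6.1.1). An imputation model without arm lets missing values in one arm borrow from the others. That does not fit the SAP's own account of missing at random in 7.3.1, given there for the repeated-measures model: participants who drop out resemble others on the same treatment. The protocol's model for the sensitivity estimand (12.3.2.1, a generalized linear mixed model) did contain treatment and treatment-by-visit terms.

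These analyses exist to show whether the primary result depends on how missing data are handled. A shift produced by the imputation model itself would be confounded with that question.

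**Working it through.** **The plan's own figure.** SAP 5.5 gives 40 participants per arm, a 10% placebo rate and a 30-point difference, "assuming an overall 2-sided alpha of 0.025". With z = 2.241 and a pooled rate of 0.25:

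- null standard error = √(2 × 0.25 × 0.75 / 40) = 0.0968
- alternative standard error = √((0.10 × 0.90 + 0.40 × 0.60) / 40) = 0.0908
- power = Φ((0.30 − 2.241 × 0.0968) / 0.0908) = Φ(0.91) = 82.0%

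This agrees with the stated power of more than 80%. It concerns the non-responder analysis and does not depend on the imputation model.

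**Bias under the literal wording.** No closed formula fits, so I used a large simulation (120,000 participants; parameter uncertainty ignored). It has seven components at Weeks 2, 4, 8 and 12, calibrated to "a placebo ACR50 response rate of 10% and a difference in ACR50 response rate of 30% between placebo and each sonelokimab dose regimen". Data were made missing completely at random, so any bias comes from the imputation model.

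Assumptions that are not in the documents:

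- correlation between components 0.3 to 0.7, and between visits 0.5 to 0.7
- treatment effect at 40, 70, 90 and 100% of its full size at the four visits
- imputation pooled over arms, with 80% of participants on active treatment (four arms of five)
- 5, 10 or 20% of participants imputed; the plan gives no missing-data rate

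ACR50 among imputed participants, placebo / active (difference), for component correlation 0.5 and visit correlation 0.7; the true values are 10% / 40% (0.300):

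| Visits missing | Separate, no arm (as worded) | Separate, with arm | Joint, no arm | Joint, with arm |
|---|---|---|---|---|
| Week 12 | 11.3 / 31.3 (0.199) | 5.7 / 34.9 (0.292) | 17.0 / 37.5 (0.205) | 9.4 / 39.6 (0.302) |
| Weeks 8 and 12 | 13.8 / 29.6 (0.158) | 5.9 / 34.7 (0.288) | 20.0 / 36.5 (0.165) | 9.7 / 39.7 (0.300) |
| All post-baseline | 17.5 / 17.3 (−0.001) | 1.0 / 26.6 (0.256) | 33.5 / 33.4 (−0.001) | 10.1 / 39.9 (0.299) |

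Over all assumed correlations, the as-worded difference among imputed participants is 0.18 to 0.20 with only Week 12 missing, 0.13 to 0.16 with Weeks 8 and 12 missing, and about 0 with no post-baseline data.

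**Effect on the trial-level difference.** With imputed fraction m, overall difference = (1 − m) × 0.30 + m × (difference among imputed). Using 0 and 0.20 as the extremes:

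| m | Lower | Upper | Loss from 30 points |
|---|---|---|---|
| 5% | 0.95 × 0.30 + 0 = 0.285 | 0.285 + 0.05 × 0.20 = 0.295 | 0.5 to 1.5 |
| 10% | 0.90 × 0.30 + 0 = 0.270 | 0.270 + 0.10 × 0.20 = 0.290 | 1 to 3 |
| 20% | 0.80 × 0.30 + 0 = 0.240 | 0.240 + 0.20 × 0.20 = 0.280 | 2 to 6 |

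For scale, one participant in an arm of 40 is 2.5 points.

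**ACR20.** With assumed rates of 25% and 60% (true difference 0.35), the as-worded model gives 0.332 to 0.345, 0.314 to 0.341 and 0.279 to 0.332 at the same three fractions.

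**Which feature does what.** With arm added but components still separate, imputed ACR50 is too low in both arms (placebo 1 to 6%, active 20 to 36%) and the overall difference is 0.279 to 0.300. For ACR20 the same model slightly raises the difference (0.351 to 0.367), so separate imputation alone has no fixed direction on the contrast. With joint components but no arm, the overall ACR50 difference is 0.238 to 0.296. With both corrected, it is 0.299 to 0.303.

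**The case against.** The strongest reply is that the prose is not the whole specification. The pseudo code belongs to the SAP, and a treatment variable or by-arm processing there would remove the larger problem. The sentence about all variables informing one another can also be read as ordinary fully conditional imputation, which fits one model per variable with the others as predictors; previous visits are not expressly limited to the same component. This stands, and it is why the point is conditional. It does not settle the matter: the sentence covers only variables that are in the model, and the visible list leaves treatment out.

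The reach is also limited. Non-response rules remove many cases from the first estimand's imputation, and protocol 9.4 asks participants who stop treatment in Part A to keep attending through Week 12. The separate-component argument does not apply to PASI90; the treatment omission does.

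A reader might infer that the imputation forces the treatment effect to zero. It does not: earlier visits carry part of the effect, and the imputed difference vanishes only for participants with no post-baseline data. A reader might also infer that the sensitivity analyses cannot inform robustness. Because the net ACR50 bias is toward the null, a favourable result from them would still be supportive.

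**Conclusion.** The point holds for SAP 8.6.1.3 as worded, subject to a check of the pseudo code. If the wording is followed, imputed ACR50 and ACR20 responses lose the correlation between components, and the arms are pulled together. The ACR50 loss is about 0.5 to 1.5 points at 5% imputed, 1 to 3 at 10% and 2 to 6 at 20%, and is greatest for participants with little post-baseline data. These sizes rest on the assumed correlations, the assumed build-up of effect over visits and the assumed missing fractions. PASI90 is affected only by the missing treatment term, and I have not sized that.

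The documents do not support a claim that the primary result is biased, or that its power or type I error is affected. Nor do they show that bias will occur, since the code is unseen. What could go wrong is interpretive: a weaker imputation-based result could be taken as fragility of the primary finding when part of the shrinkage comes from the imputation model.

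**What to change.** In SAP 8.6.1.3, state that:

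- the imputation includes randomized arm, or is run separately by arm;
- all seven ACR components at all visits enter one fully conditional model as mutual predictors, with sex and prior biologic exposure;
- ACR50 and ACR20 are derived afterwards in each completed dataset;
- the PASI imputation also includes treatment.

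Then confirm that the pseudo code matches. If it already does, only the wording changes. Otherwise the cost is a modest programming change and a convergence check. Seven components over several visits is a large model for about 200 participants, so a simpler predictor set should be named in advance as the fallback if the full model does not converge.

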#### **8.6.1.4 Multiplicity**

The following multiplicity adjustments will be used to control the overall type I error rate at 0.05 for the primary endpoint and key secondary endpoints. All sensitivity analyses will be regarded as exploratory and no formal adjustment for multiplicity will be made.

#### **Primary Endpoints**

To adjust for multiple testing and to control the family-wise error rate, the Bonferroni-Holm method will be applied first to sonelokimab 120 mg Q2W (Arm 1) and sonelokimab 60 mg Q2W (Arm 2), followed by a step-down procedure to test for sonelokimab 60 mg Q4W (Arm 3).

The Bonferroni-Holm procedure will work as follows:

- 1) Let  $p_{\text{SLK120mg,Q2W}}$  and  $p_{\text{SLK60mg,Q2W}}$  be the p-value resulting from the comparison between sonelokimab 120 mg,Q2W vs placebo and sonelokimab 60 mg,Q2W vs placebo groups respectively.
- 2) If the smallest p-value obtained in step 1 is greater than or equal to  $\alpha/2 = 0.025$ , the procedure is stopped and no p-values are significant.
- 3) If the smallest p-value is declared significant (i.e p-value less than  $\alpha/2 = 0.025$ ), then compare the largest p-value with  $\alpha = 0.05$ . If the p-value is less than 0.05, then declared as significant. Otherwise not significant.
- 4) If both  $p_{\text{SLK120mg,Q2W}}$  and  $p_{\text{SLK60mg,Q2W}}$  are significant then the testing procedure will continue with the key secondary endpoints. The Bonferroni-Holm procedure used for the primary endpoint will be applied to each key secondary endpoint sequentially.
- 5) If the procedure passes all the key secondary endpoints for both doses (Arm 1 and Arm 2), then sonelokimab 60 mg Q4W (Arm 3) will be compared to  $\alpha = 0.05$  first for the primary endpoint and then sequentially through the key secondary endpoints.

### 8.6.1.5 Treatment-by-Center Interaction Analysis (Multi-Center Study)

Unless otherwise specified, data from all investigational centers/sites will be pooled for analyses.

## 8.6.2 Analysis of Primary Efficacy Endpoint

The primary analysis will be performed using the FAS.

All sensitivity analyses will be performed using FAS population. Summaries for Part B will be performed using the FAS-B population.

### 8.6.2.1 American College of Rheumatology 50 Clinical Response

The ACR50 will be assessed at Week 2, Week 4, Week 8, Week 12, Week 14, Week 16, Week 20 and Week 24 however the primary endpoint is the proportion of ACR50 responders at Week 12.

ACR50 response criteria is defined as:

- ACR50 Responder: *participant who had improvement in the ACR response criteria  $\geq 50\%$ ;*
- ACR50 Non-responder: *Otherwise.*

ACR50 response is:

- At least a 50% improvement in TJC68;
- At least a 50% improvement in SJC66;
- At least a 50% improvement in at least 3 of the following 5 variables:

- PtAAP;
- PtGADA;
- PhGADA;
- HAQ-DI;
- hs-CRP.

A Non-responder imputation method will be used for all missing data for the primary estimand as detailed in [section 7.3.2](#).

The null hypotheses to be tested are that the proportion of ACR50 responders at Week 12 are no different for the following comparisons:

- sonelokimab 120 mg Q2W versus placebo
- sonelokimab 60 mg Q2W versus placebo
- sonelokimab 60 mg Q4W versus placebo

To test these hypotheses, a pairwise stratified logistic regression will be used as detailed in [Section 8.6.1.1](#). This analysis will also be conducted for Weeks 2, 4 and 8.

The data for Part B will be presented by FAS-Part B and will be split by Part A and Part B treatment.. Non-responder imputation and As-Observed summaries will be presented. No statistical analysis will be presented. These results will also be presented in a line plot.

The following sensitivity analysis of the Part A data will be presented:

- the first sensitivity estimand will be analysed using logistic regression, with the same covariates as for the primary analysis. Missing data will be imputed as described in [section 5.2](#) with multiple imputation applied as described in [8.6.1.3](#) such that subjects who had prohibited medication or discontinued due to efficacy or adverse events are set as non-responders, all other missing data is imputed with multiple imputation methods.
- the second sensitivity estimand will be analysed using logistic regression, with the same covariates as for the primary analysis [with multiple imputation applied as described in 8.6.1.3](#)
- An observed analysis using logistic regression model but with no imputation of missing data.

Line plots for ACR50 response rate by week will also be provided, with week on the x axis and ACR50 response rate on the y axis. Graphs for Part A and Part B (FAS) will be presented.

The responders by visit and treatment group will be summarized descriptively for Part A and Part B

The change from baseline for each component of the ACR endpoint will be analyzed using the method described in 8.6.1.2, Descriptive summaries by treatment group and visit will also be displayed for Part A and Part B.

For Part A and B there will also be a NRI/LOCF analysis. Subjects who completed the study at Week 12 due to country-specific protocol requirements (US participants) or subjects who switched arm at Week 12 will have their Part B scheduled visits be imputed with LOCF from their Week 12 visits. All

other missing data is imputed as a non-response. A summary of the number of responders by Part A treatment arm for all scheduled visits will be displayed.

#### **8.6.2.2 TJC68**

The total number of tender joints from the 2 temporomandibular, 2 sternoclavicular, 2 acromioclavicular joints, 2 shoulders, 2 elbows, 2 wrists, 10 metacarpophalangeal, 10 proximal interphalangeal, 8 distal interphalangeal joints of the hands, the 2 hips, 2 knees, 2 ankles, 2 mid-tarsal, 10 metatarsophalangeal, and 10 proximal interphalangeal joints of the feet.

#### **8.6.2.3 SJC66:**

The total number of swollen joints from the same joints as assessed for tenderness, excluding the hip joints.

#### **8.6.2.4 Health Assessment Questionnaire (HAQ-DI)**

The health assessment questionnaire (HAQ-DI) is a twenty-item PRO instrument which assesses current physical function/disability. It covers 8 categories (dressing and grooming, hygiene, arising, reach, eating, grip, walking and common daily activities). There are 4 response options ranging from 0 (no difficulty) to 3 (unable to do) (See [Appendix A](#)).

To calculate the HAQ-DI, the highest sub-category score determines the value for each category, unless aids or devices are used. There must be at least 6 out of 8 categories answered or else the score cannot be calculated. Each category scored is averaged into an overall HAQ-DI score ranging from 0 to 3.

The aids used for adjustment by category are: dressing – devices used for dressing; rising – built up or special chars; eating – built up or special utensils; walking – canes, walkers or crutches; hygiene – raised toilet seats, bathtub seats, bathtub bars, long handles appliances in bathroom; reach – long-handled appliances for reaching; and grip – jar openers.

If an aid is required for any category, or another person is required to help for any category then that category score increases a score of 0 or 1 to a 2. Scores already at 2 and 3 are not modified. Aids and devices considered recorded in the ‘other’ category will not be considered in the analysis.

Scores of 0 to 1 represent mild to moderate disability, 1 to 2 represent moderate to severe disability and 2 to 3 indicate severe to very severe disability.

#### **8.6.2.5 Patients Assessment of Arthritis pain**

The patients’ assessment of arthritis pain (PtAAP) is a self-administered pain visual analogue score (VAS). It is performed using a horizontal 100mm VAS, ranging from 0 (no pain) to 100 (severe pain) after the question: “Please indicate with a vertical mark ( | ) through the horizontal line the most pain you had from your psoriatic arthritis today. (See [Appendix B](#))

#### **8.6.2.6 Patients Global Assessment of Disease Activity**

The patients global assessment of disease activity (PtGADA) is self-administered and performed using a horizontal 100mm VAS ranging from 0 (very well) to 100 (very poor) after the question “Considering

all the ways PsA affects you, please indicate with a vertical mark ( | ) through the horizontal line how well you are doing today.” (See [Appendix C](#))

#### **8.6.2.7 Physician’s Global Assessment of Disease Activity**

The physician’s global assessment of disease activity (PhGADA) is assessed by the investigator or a qualified designee on a VAS ranging from 0 (very well) to 100 (very poor). (See [Appendix D](#))

